### Analytical approaches

#### Sample size

The study is powered to detect a significant difference in hospital LOS between patients who receive the ENRICH-US intervention (cases) and patients who receive standard post-operative care (controls). Calculation of the anticipated power was based on the design effect of a stepped wedge, clustered randomized controlled study [44]. The design effect is based on the number of clusters, the intra-cluster correlation coefficient, and the average cluster size per period. A total of 18 hospitals participating in the PedSRC agreed to participate in the study. Prior data indicates that approximately 616 GI surgeries are performed annually across the sites, for an average of 34 surgeries per site (range 5–120 patients per site per year). Overall, a sample of an average of 20 patients per site provides > 80% power to detect a difference in LOS of at least 1.25 days, and a 60% enrollment rate will yield an adequate sample for this study.

#### Statistical analysis of Aim 1

Descriptive statistics will be calculated for all variables of interest and include means with standard deviations, medians and ranges, or counts and percentages, as appropriate. Characteristics of the clusters and of patients within each cluster will be summarized by group of stratification randomization. Effect sizes will be used to quantify the degree of clinical effectiveness for the primary outcome (LOS) and secondary outcomes.

The primary analytic approach is the use of generalized linear mixed models (GLMM). These models allow for the estimation of both fixed effects (e.g., intervention, cluster) and random effects which include the variation of individual clusters around the conditional mean of the clusters [45]. Models will include a hospital-specific random intercept, using an unstructured covariance matrix, if possible. Two-level (patients/hospital) and three-level (patients/physicians/hospitals) models will be considered in the analysis, when possible. Appropriate modeling assumptions will be verified, and data may be transformed (e.g., logarithm, square-root) to meet model assumptions. All effect sizes (e.g., difference in means, rates) will be presented with associated 95% confidence intervals. Because calendar time may be associated with both exposure to the intervention and, possibly the outcome, it will be included as a potential confounder in all analyses. In addition, the length of the period during which the cluster has been exposed to the intervention will be analyzed as a possible effect modifier [46].

In our primary analysis, patients will be classified into treatment groups, based on each site’s randomized crossover time and analyzed, using the intention to treat principle. In a sensitivity analysis, we will examine the effect of the ENRICH-US intervention “dose” by using the number of elements delivered to a patient, as a treatment adherence measure. Heterogeneity of treatment effects (HTE) will be examined, using a within-cluster comparison of exposed and unexposed periods which will help to identify clusters and cluster characteristics that may inform aspects of the adaptation and sustainability. The analysis will be conducted using SAS v. 9.4 (Cary, NC) and R v.3.2.2 (Vienna, Austria), and the statistical significance level will be considered 0.05 unless otherwise noted.

#### Qualitative analysis of Aim 2

The LC meeting recordings and semi-structured interview transcripts will be coded and analyzed thematically, using a hybrid form of textual analysis which combines inductive and deductive logics, and informed by the tasks at hand (implementation of ENRICH-US intervention, degree of implementation fidelity, site-specific, contextual adaptations), as well as, allowing for unanticipated themes and subject perspectives to emerge, as in our prior work [47–50]. A computer-assisted qualitative data analysis software (MAXQDA) will be used with initial categorical themes being entered and applied to further transcripts. Emerging themes will be iteratively checked with the interviewees to ensure the accuracy, completeness, and perceived validity.

The DCC will use qualitative comparative analysis (QCA) to combine the qualitative and quantitative data and determine the necessary and sufficient conditions for successful implementation [51, 52]. QCA answers the question: What conditions, alone or in combination with other conditions, are necessary or sufficient to produce the outcome of interest? QCA is a case-oriented, mixed-methods approach of analysis that examines relationships between conditions and an outcome of interest, which captures the complexity of implementing QI interventions. Accordingly, QCA allows for systematic, cross-case comparison of data for implementation purposes [53]. For the QCA analysis, quantitative data, such as hospital setting (e.g., rural), bed size, number of surgeons, and case volumes, will be merged with the qualitative results. Using QCA, we will be able to identify the causal pathways to the outcome(s) of interest and identify conjunctional causation or the conditions that may only display their effects in conjunction with other conditions [54].

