**Fig. 2 Fig2:**
[figure not shown]
Hybrid study design with equal focus on clinical effectiveness and implementation

The study will facilitate contextual adaptation with rapid-cycle small tests of change using a LC approach that includes patient/parent stakeholders and sustainable and high fidelity implementation by applying the National Implementation Research Network’s five Active Implementation Frameworks AIFs (Fig. 3), which identify competency, organization, and leadership as drivers of implementation and empower team collaboration and evaluation [30]. The study is a pragmatic clinical trial, which will take place in the real clinical setting where patients receive usual care by their usual clinicians with data captured primarily from existing data sources, such as electronic health records (EHRs) and minimal study eligibility criteria for recruitment of pediatric patients undergoing non-emergent GI surgery [31]. The nature of this trial does not allow for subjects (patients or clinicians) to be blinded.

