**Fig. 5 Fig5:**
[figure not shown]
Time schedule of enrollment for participants

To improve the generalizability of the study’s findings, the study purposefully included diverse sites, including some low-volume pediatric surgical sites. Exploring implementation obstacles unique to low volume sites will facilitate future dissemination efforts beyond the participating sites. To reduce the potential bias of surgery volume among the sites, a stratification randomization schema will be used [35]. Based on our initial assessment of surgical volumes, there are 12 high-volume sites (range 20–120 cases/year) and 6 low-volume sites (< 20 cases per year). Thus, we propose to employ a stratification randomization schema such that each of the 3 clusters has 4 high-volume sites and is limited to 2 low-volume sites.

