### Data collection

For Aim 1, the Northwestern University (NU) Data Coordinating Center (DCC) will work closely with each site’s PI and coordinator to set-up access to data collection tools in the Research Electronic Data Capture (REDCap) system. The DCC will provide web-based training tutorials. Only the site PI, coordinator, and data abstractors will be able to identify patients at their site. Extensive training will prepare each site’s coordinator/data abstractor to monitor enrollment, enrollment targets, and compliance with eligibility criteria; monitor completion of data collection and send additional reminders; and produce performance reports for the monthly LC video-conference meeting (e.g., enrollment per month, compliance with the ENRICH-US intervention elements). Coordinators/data abstractors will be provided with a data dictionary with definitions of all study measures.

Measures include patient demographic (e.g., age, sex, race/ethnicity) and surgery-specific information (e.g., surgeon, diagnosis). At the start of the study data collection, the first five cases at each site will be used to assess data quality and any additional training needs, in close collaboration with the DCC. Coordinators/data abstractors will also receive training on the collection of HRQoL assessments (pre-, 2–5 days post-, and 4–6 weeks post-operatively). Sites will provide support for patients/parents who will be asked to complete the REDCap-based surveys by telephone, iPad, or computer with paper versions available, as needed.

For Aim 2, implementation metrics and contextual factors needing adaptations will be collected by recording the monthly LC video-conference meetings. Qualitative methods will be used to categorize key adaptation themes and implementation strategies. Additional semi-structured interviews will be conducted by the research team with each site PI and coordinator.

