#### Oversight and monitoring

A Data Safety and Monitoring Board (DSMB) will ensure the safety of subjects and the validity and credibility of the trial. This board will include an experienced pediatric gastroenterologist, a pediatric surgeon, and a patient or parent of a patient who underwent GI surgery. All board members are not involved in the study and are free of competing interests. Interim analyses will be conducted every 7 months and include any potential adverse events (event rates), timing and completeness of data collection, adequacy of sample size, comparability of treatment clusters [35]. The DSMB can ask for more frequent reporting if concerns arise. Approximately 2 weeks before the DSMB meeting, the study statistician will send a report to the DSMB members that includes patient recruitment, ratio of consent to randomization, attrition, and any adverse events by treatment, labeled A or B. While the study is not blinded by design, the data will be presented in a blinded fashion to reduce any bias associated with knowing the intervention cohort. The board will review the results and assure that the conduct of the trial is acceptable. Any recommendations of the committee will be directly made to the Co-Principle Investigators. The trial will be stopped if the committee identifies any significant safety concern which warrants stopping the trial.

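### Enrolled case mix can shift when a site crosses over; the stated model gives age, diagnosis and volume stratum no role, and the DSMB consent ratio does not fit a site-randomised trial

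*Protocol article*

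**What the plan says.** **Model.** Under Statistical analysis of Aim 1, the article describes generalized linear mixed models: "These models allow for the estimation of both fixed effects (e.g., intervention, cluster"). It continues: "Models will include a hospital-specific random intercept, using an unstructured covariance matrix, if possible". Of calendar time it says that "it will be included as a potential confounder in all analyses". Length of exposure is to be examined as an effect modifier, and patients are classified by their site's randomised crossover time under intention to treat. A three-level model with physicians is to be considered when possible.

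**Stratum.** Randomization and timeline states that "a stratification randomization schema will be used", so that "each of the 3 clusters has 4 high-volume sites and is limited to 2 low-volume sites". The only analytic use named for the stratum is a descriptive summary.

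**Data.** Data collection lists age, sex and race/ethnicity, and "surgery-specific information (e.g., surgeon, diagnosis").

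**Recruitment.** Trial design and setting says that the trial "does not allow for subjects (patients or clinicians) to be blinded". The consent section gives screening, recruitment and consent to site team members. Installation phase puts the site PI and coordinator on the implementation team, which is formed 6 to 9 months before the cluster's start period.

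**Monitoring.** Oversight and monitoring lists, among the items reported to the DSMB, the "ratio of consent to randomization".

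**The concern.** Randomisation balances hospitals over start dates. It does not balance the patients who agree to take part before and after a hospital crosses over. Those who recruit know which phase the site is in, and coordinators also report compliance with the ENRICH-US elements. If simpler cases are enrolled more readily after crossover, mean length of stay falls without any effect of the intervention. The population leaves room for this: it is mainly but not only inflammatory bowel disease, and covers Crohn's disease, ulcerative colitis and other elective GI surgery.

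The article does discuss confounding, but the controls it names are aimed elsewhere. Calendar time is shared by all hospitals, so it does not absorb a change that occurs at each hospital's own crossover. A random intercept is constant over time within a hospital. Intention to treat governs how enrolled patients are classified, not who is enrolled. The monitoring item that should reveal differential consent has a denominator that does not exist at patient level.

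**Working it through.** **1. The plan's own figures.** 616 / 18 = 34.2 surgeries per site per year, and 34.2 × 0.60 = 20.5. The 60% rate thus reproduces the average of 20 per site if that is read as per site-year. The stated power above 80% for 1.25 days can be neither reproduced nor refuted, because the SD of length of stay and the ICC are not given. With a stepped-wedge variance formula, ICC 0.01 to 0.20 and two-sided 5%, it holds up to an SD of about 2.6–2.8 days (20 per site in total), 3.5–4.0 days (per site-year) or 4.8–5.2 days (per site-period).

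**2. Size of a selection effect (all inputs assumed).** Suppose 40% of eligible patients are complex and 60% of all patients enrol in both phases. Before crossover both types enrol at 60%; afterwards complex patients enrol at rate e. Complex share among enrolled = 0.40 × e / 0.60. Bias = (that share − 0.40) × difference in length of stay.

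| e after crossover | Complex share | Bias, 1-day difference | 2 days | 3 days |
|---|---|---|---|---|
| 0.55 | 0.367 | −0.03 | −0.07 | −0.10 |
| 0.50 | 0.333 | −0.07 | −0.13 | −0.20 |
| 0.40 | 0.267 | −0.13 | −0.27 | −0.40 |

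Against 1.25 days the range is 0.033 / 1.25 = 3% to 0.40 / 1.25 = 32%.

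**3. Does adjustment help?** A 400-run simulation had true effect 0, e = 0.50 and a 2-day difference. It used period effects, hospital random intercepts and 12 larger and 6 smaller hospitals. Mean estimates were:
- no adjustment: −0.11 day (SE 0.53)
- with stratum: −0.11 day (SE 0.52)
- with stratum and case mix: 0.03 day (SE 0.51)

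The Monte Carlo SE is about 0.53 / √400 = 0.03. Case mix removes the bias here because the variable that drives selection is measured; the stratum does nothing to it.

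**4. Precision (assumed SD 4 days, ICC 0.05, 10 per site per half-year, 4 half-years).** Three sequences of 6 hospitals cross over at half-years 2, 3 and 4. The stepped-wedge variance is

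Var = I·s²(s² + Tτ²) / [(IU − W)s² + (U² + ITU − TW − IV)τ²]

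with I = 18, T = 4, U = 36, W = 504, V = 84, τ² = 0.8 and s² = 15.2 / 10 = 1.52.

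- Base: 18 × 1.52 × 4.72 / (144 × 1.52 + 360 × 0.8) = 129.1 / 506.9 = 0.255, so SE 0.505 and power 70%.
- Case mix with R² = 0.2: s² = 1.216, so 96.7 / 463.1 = 0.209, SE 0.457. The ratio is 0.905 and power 78%.
- R² = 0.1 and 0.3: ratios 0.954 and 0.852, power 74% and 83%.
- Stratum explaining half of the between-hospital variance: τ² = 0.4, so 85.4 / 362.9 = 0.235, SE 0.485. The ratio is 0.961.

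Over ICC 0.01 to 0.20, 5 or 10 per half-year and 4 or 7 half-years, case mix lowers the SE by about 5% (R² 0.1) to 15–16% (R² 0.3). The stratum, explaining 25–50% of between-hospital variance, lowers it by 0.2–4%.

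**The case against.** The strongest reply is that the article is silent rather than wrong. Its list of fixed effects is introduced as an example, and covariate lists are commonly left to an SAP or full protocol, neither of which is shown. A reader might infer that the plan excludes adjustment for stratum and case mix; the text does not say so, and surgeon may enter through the three-level model. This stands, and it limits the point to the confounding control that the article does state.

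Other readings also go too far:
- That leaving the stratum unnamed causes bias. Volume is a hospital-level factor balanced 4:2 in every cluster, with a hospital random intercept in the model. Its absence costs little precision and has no bearing on patient selection.
- That 40% of patients are expected to be missed. The article calls 60% enrolment adequate; it does not forecast it.
- That differential consent would go wholly unseen. The DSMB also receives recruitment, attrition and comparability of clusters, coordinators report enrolment per month, and the DCC verifies consent and enrolment monthly and quarterly. These could show a change in numbers at crossover. None is described as consent among eligible patients by phase.
- That the change is free. Procedure class and counts of eligible patients who do not enrol are not listed as collected.

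The reply does not remove two things: the stated controls do not address selection at crossover, and the DSMB ratio is wrong as written for a trial that randomises sites.

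**Conclusion.** The point holds in a limited form. Unblinded individual consent after site allocation leaves a route for case mix to shift at crossover. Calendar time, the hospital intercept and intention to treat do not close it, and age and diagnosis, which are collected, have no stated role in the primary model. The consent-to-randomisation ratio cannot be computed for patients.

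The size is uncertain, because no SD, ICC, R² or selection rate comes from the article. Under the assumed inputs the bias runs from 0.03 to 0.40 day; in the simulated case it was 0.11 day, about a fifth of its standard error. The likely gain in precision is 5–16% from case mix and 0.2–4% from the stratum. A reader might infer that adjustment would abolish selection bias, but it removes only what measured covariates carry. That is why the monitoring change matters alongside it. The article does not show that selection will occur, only that the plan as worded is poorly placed to detect or correct it.

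**What to change.** 1. In Statistical analysis of Aim 1, prespecify as fixed effects in the primary model: age, diagnosis (Crohn's disease, ulcerative colitis, other), procedure class if it is recorded, and the volume stratum. Settle this before outcome data are examined. Do not adjust for surgical approach: Table 1 lists minimally invasive technique as an element of ENRICH-US, so adjusting for it would take out part of the effect being estimated. If a detailed analysis plan already names these covariates, a cross-reference is enough.

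2. In Oversight and monitoring, replace the consent-to-randomisation ratio with patients consented over eligible patients screened, by site and by phase.

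The cost is small: a few more model parameters, and a count of eligible patients screened at each site if this is not already kept.

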### Trial management

#### Roles and responsibilities

The study sponsor/management and DCC is located at Northwestern University (NU). The DCC research team will perform study management tasks such as site management and contracting, central Institutional Review Board (cIRB) submissions and oversight, creation of the data entry database, trial-wide communication, orchestration of site PI and coordinator training activities, coordination of site initiation, creation and delivery of LC meeting webinars about the ENRICH-US intervention, leading the monthly LC meetings during the implementation phases for each cluster, and performing all data analyses. Monitoring will be performed by the DCC centrally. The DCC uses web-based data validation rules, data manager assurance of data collection through independent double entry, routine statistical analysis, and on-going review of site metrics. Remote monitoring will include verification of written consent and study enrollment, by monthly and quarterly periods. To verify informed consent forms of enrolled subjects, sites will upload an electronic portable document format (PDF) of the signed consent form into the password-protected REDCap database. The PDF file will be linked to the subject identification and stored on a secure server behind the NU firewall. The files on these servers can only be accessed by designated study personnel upon entry of a password. The DCC will remotely monitor the informed consent forms and any identified issues will be relayed to the site for corrective and preventive action. Significant protocol amendments will be addressed with the study’s funding agency first, and then submitted to the cIRB for approval. Minor protocol amendments will also be submitted to the cIRB for approval and distributed to the sites, thereafter. Additionally, the protocol will be updated in the clinical trial registry.

#### Data quality assurance and quality control

Routine data audits will be performed to monitor data completion and integrity by the DCC. The DCC will verify data for a random sample of 10% of enrolled patients at each site. Data quality assurance processes at the DCC include logic and rule checks built into the REDCap database and real-time central monitoring. Quality control (QC) procedures will be implemented beginning with the data entry system, and data QC checks that will be run on the database will be generated. Any missing data or data anomalies will be communicated to the site(s) for clarification/resolution.

#### Ethical considerations and data security

All investigators will ensure that the study is conducted in full conformity with Regulations for the Protection of Human Subjects of Research codified in 45 CFR Part 46, 21 CFR Part 50, and/or 21 CFR Part 56.

Pediatric GI surgeries have complication rates of 20 to 40% [55, 56]. While each of the ENRICH-US intervention elements has some inherent risk, patients were purposefully selected as study subjects because they most closely resemble adult patients for whom the safety of ERPs has been well established. In addition, all participating surgeons retain the right to deviate from the ENRICH-US intervention for any clinical need. While consent/assent will be obtained from patients and their parent/legal guardian, they will retain the right to withdraw from the study at any time without any effect on their healthcare.

To avoid the identification of individual patients, all data feedback to sites will be performed in an aggregate fashion. While site level-performance measures will be used during the LC meetings and iterative processes of improving implementation, patient-level and provider/surgeon-level data will only be provided and/or discussed with each site. Similarly, any peer-review publications or subsequent dissemination of results will only include aggregate results reported by site, with all sites remaining anonymous.

Data Security is of the upmost importance and the DCC, under the purview of the two Co-PIs, will assume responsibility for the Data Security Plan. All data collected in the REDCap system will be initially stored securely in the NU enterprise data warehouse (EDW), which is HIPAA-compliant. Subsequent data downloads from the EDW for use by the DCC will be stored on research servers that have restricted access and require institutional login and passwords. Similarly, all audio recordings and transcriptions of audio from interviews and WebEx sessions will be saved in secure research servers at NU.

Two Co-PIs are responsible for granting data access only to DCC staff critical to the conduct of the study. For data backup and recovery, all source study data are stored on secure serves at NU and within the NU EDW. These systems have backup and recovery systems in place in case of equipment malfunction, physical facilities impairment, or natural disaster.

